#### Child recruitment

Once teachers have identified the children eligible to take part in the trial, the teacher will distribute paper information sheets and consent forms to their parents/carers. Translated versions will be offered for parents with English as an additional language (EAL). The participant information sheets will be supplied to schools by the research team, along with a simplified illustrated information sheet for children to read together with their parents/carers. The information sheets and consent forms will be tailored to Focal and Partner children. Schools will be asked to send a reminder to parents/carers if no response is received approximately two weeks after receipt of the original invitation pack. Completed consent forms are to be returned to the school for collection by the research team.

#### Child consent procedure

All parents will be given the option to speak to a member of the research team or to contact the Chief Investigator in the event of additional questions. Consent to enter the study will be sought from each participant only after a full explanation has been given, an information leaflet offered and time allowed for consideration.

Participation in the study will be entirely voluntary and written informed consent from parents/carers will be obtained before child baseline data is collected and randomisation is conducted. On the consent form, parents/carers will be requested to consent for their child’s school to provide data including child’s name, date of birth, gender, home postcode, ethnicity, religion/belief, English as an additional language (EAL), education, health and care plan (EHCP) status, help received from a Speech & Language Therapist and/or an Educational Psychologist and receipt of Pupil premium and/or free school meals (FSM, a proxy for deprivation) for the purposes of sample description and potentially for use as covariates in analyses. The consent form for Focal children will also request parent/carers to provide their educational qualifications, employment status, ethnicity and consent/commitment to complete the EQ-5D-Y (proxy version 1), CHU-9D, and resource use data questionnaires at specified time-points. Parents/carers will return completed consent forms to the school.

#### Child and parent/carer retention and withdrawal

At the end of the trial and following completion of all questionnaires, parents/carers of Focal children will receive a £15 voucher to offset any incidental expenses and in recognition of their participation.

All participants are free to withdraw at any time from either the intervention or follow-up data collection without giving reasons and without prejudicing further care. The Chief Investigator will preserve the confidentiality of participants taking part in the study and is registered under the Data Protection Act. If a child does not appear to want to take part at the time the E-PLAYS intervention is being delivered and/or assessments are taking place, their wishes will be respected. Where a parent/carer wishes to withdraw from the study, it will be clarified as to whether they wish their child to withdraw from the intervention or if they themselves wish to withdraw (i.e., stop completing outcome measures). Where withdrawal is only for the participating parent/carer, the child may continue to take part in all other aspects of the trial and follow-up data will continue to be collected when possible. If a Partner child withdraws, another child from the school will be recruited as a replacement for the purposes of intervention delivery.

#### Teaching assistant recruitment

All teaching assistants will be asked to provide information at baseline on their work training and experience. School staff will also be asked to complete a survey exploring usual care for children with social communication difficulties. A subset of teaching assistants will be asked to participate in interviews, observations and focus groups; for these a separate information sheet and consent form will be provided by the research team.

#### Teaching assistant retention and withdrawal

Where withdrawal is only for the teaching assistant, we will ask schools to replace them for the intervention period. Where a teaching assistant cannot be replaced, the study team will discuss the implications of this with affected participant(s) to establish if they wish to continue providing outcome data.

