### Child eligibility (Focal children)

Focal child eligibility criteria are as follows:Children aged 5–7 years old;Children who meet the criteria for social communication difficulties as determined by the Social Communication Behaviour Checklist [24];Children whose parents/carers give consent for them to take part in the E-PLAYS-2 trial;Children who have not used E-PLAYS before;Children whose parents/carers are willing to complete relevant questionnaires;Children who complete the key trial baseline assessments (assuming all other eligibility criteria are met);

Baseline and outcome data will be sought for all Focal children (subject to potential withdrawals from some or all aspects of follow-up data collection by participating schools or parents).

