### Intervention

The E-PLAYS programme is designed for children with SCDs aged 5–7 years old (referred to hereafter as ‘Focal’ children). Using a computer game, E-PLAYS guides the Focal child through real-life conversational exchanges with a specific focus on (a) requesting optimally useful information (b) giving helpful directions and (c) asking for clarification. Each Focal child is matched with a ‘Partner’; a typically-developing child from the same year group.

Each E-PLAYS session uses the computer game which is designed for two players using interlinked laptops. There are ten weekly sessions of 30 min each; schools’ teaching assistants are trained to deliver and supervise all sessions. Five sessions are with the Focal child and the teaching assistant only, five are with the Focal and Partner child together supervised by the teaching assistant. Sessions with the classmate (Partner child) give the child an opportunity to practice newly-acquired skills and also to learn collaboration skills through joint problem-solving with a peer. E-PLAYS is web-based, enabling us to distribute E-PLAYS directly to schools. Teaching assistants will self-train using a comprehensive manual with online support. The E-PLAYS software automatically records the number of sessions along with date accessed and sends this data directly to the research team.

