### Statistical analysis plan

Statistical analysis will primarily be conducted in Stata/MP v18 [35] or later, unless specified otherwise. All analyses will be conducted just once at the end of the trial follow-up period, according to precise specifications detailed in a Statistical Analysis Plan (SAP) that will be approved by the TMG and TSC prior to the end of follow-up. Any departures from the analysis plan will be reported and justified in the final trial reports and other relevant published articles.

The flow of clusters and participants through the study will be presented according to CONSORT guidance for cluster RCTs. Continuous characteristics will be summarised in terms of the available sample size, arithmetic mean, standard deviation, median, interquartile range, minimum and maximum. Categorical characteristics will be summarised in terms of frequencies and percentages.

For all between group comparisons, clusters and participants (both Focal and Partner) will be analysed as part of the groups to which they were randomised, regardless of subsequent engagement with the allocated treatment. All analyses estimating between group contrasts will include all participants with data available for the relevant outcome (unless explicitly stated otherwise in the SAP). Point estimates of contrasts between randomised groups will be reported together with appropriate 95% confidence intervals. Point and interval estimates will be reported on the scale of the original measurements (as well as the scale used for the analysis should these differ). P-values for statistical tests will be two-sided unless specified otherwise in the SAP.

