### Principal stratum analyses (Focal children)

Participants allocated to the control group will not have access to the E-PLAYS intervention. Participants allocated to the intervention group will be offered the E-PLAYS intervention, but may not receive any sessions at all, or may receive only a proportion of the planned ten sessions (or potentially none of them).

We will estimate two different CACE estimands under different definitions of compliance: (1) The difference in expected TPS mean composite score at 35–40 weeks among participants that would complete at least one session of the E-PLAYS programme if they were randomised to E-PLAYS; (2) The difference in expected TPS mean composite score at 35–40 weeks among participants that would complete at least seven E-PLAYS sessions (70% of the programme) if they were randomised to E-PLAYS.

We will use instrumental variable estimators to estimate both of these principal stratum estimands. Specifically, we will use random allocation as an instrument for the relevant definitions of treatment receipt in each case, with estimation performed using a generalised two-stage least squares random effects estimator. These analyses will include the same baseline covariates as included in the primary analysis and random intercepts for school cluster. Point estimates of the two principal stratum estimands outlined above will be reported together with two-sided 95% confidence intervals and p-values for tests of H_0_: $$\delta$$ = 0.

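### Asking families about leaving follow-up when a teaching assistant cannot be replaced opens a route to outcome loss in the intervention arm only, tied to non-delivery

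*Protocol article*

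**What the plan says.** The protocol article, under Teaching assistant retention and withdrawal, gives two steps. First, "Where withdrawal is only for the teaching assistant, we will ask schools to replace them for the intervention period". If that fails, "the study team will discuss the implications of this with affected participant(s) to establish if they wish to continue providing outcome data".

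Four other parts bear on this.

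- **Delivery.** Under Intervention, "teaching assistants are trained to deliver and supervise all sessions". Under Principal stratum analyses, "Participants allocated to the control group will not have access to the E-PLAYS intervention".
- **Follow-up.** Under Child eligibility (Focal children), "Baseline and outcome data will be sought for all Focal children", subject to withdrawals. The section on child and parent/carer retention and withdrawal requires the team to find out whether a family is leaving the intervention or leaving data collection, and treats these as different events.
- **Analysis.** Under Statistical analysis plan, clusters and participants "will be analysed as part of the groups to which they were randomised, regardless of subsequent engagement with the allocated treatment". The same section adds: "All analyses estimating between group contrasts will include all participants with data available for the relevant outcome".
- **Primary model.** The listed terms are group, time point and their interaction, baseline TPS, year group, free-school-meal status, location and a school random intercept. Sessions received is not among them.

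**The concern.** The second step links a failure of delivery to a question about leaving data collection. Loss of the assistant does not stop the outcome from being measured, because a blinded research assistant administers the TPS. The children who would be asked are those who received little or none of the programme, and an intention-to-treat comparison needs to keep them. The control arm has no matching prompt.

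If some of these families stop, the observed intervention arm contains a larger share of children who received E-PLAYS than the randomised arm does. The estimate then moves away from the effect of being allocated to E-PLAYS and towards the effect among those who received it. Missing-at-random estimation does not correct this, because session receipt is not in the model. The programme is ten weekly sessions, so loss of an assistant would usually come before the 15–20-week visit. A child who leaves at that stage may have no post-randomisation TPS score and would contribute nothing to the model.

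**Working it through.** **1. Does the prompt act in one arm?** Assistants deliver all sessions, control children have no access to E-PLAYS, and replacement is sought for the intervention period. A control child therefore has no delivery to lose, and the prompt arises in practice only in intervention schools.

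**2. The plan's own figure.** Inputs from the Sample size section (Revised): difference 2, SD 7, pre-post correlation 0.6, ICC 0.05, 44 schools per arm, 4.55 children per school, 20% attrition.

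- Children per school after attrition: 4.55 × 0.8 = 3.64
- Design effect: 1 + (3.64 − 1) × 0.05 = 1.132
- Residual variance: 49 × (1 − 0.36) = 31.36
- Variance per arm: 31.36 × 1.132 / (44 × 3.64) = 0.2217
- SE of the difference: √(2 × 0.2217) = 0.666
- Power: Φ(2/0.666 − 1.96) = 85.2%, which matches the stated 85.2%

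**3. Is power the problem?** Keep control attrition at 20% and raise it in the intervention arm only:

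| Intervention-arm attrition (assumed) | Power |
|---|---|
| 25% | 84.2% |
| 30% | 83.1% |
| 35% | 81.8% |
| 40% | 80.3% |

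The loss of power is small, so the issue is bias.

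**4. Illustration of bias.** The protocol gives no rate of unreplaceable assistant loss and no rate of families stopping, so both are assumed. Let q be the share of intervention children affected, w the share of these who stop giving data, and D = 2 the effect if delivered. Assume no effect if not delivered and equal prognosis.

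- Intention-to-treat value: D(1 − q)
- Value expected from available data: D(1 − q)/(1 − qw)

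| q | w | Intention-to-treat | Available data | Excess |
|---|---|---|---|---|
| 5% | half | 1.90 | 1.95 | 0.05 |
| 5% | all | 1.90 | 2.00 | 0.10 |
| 10% | half | 1.80 | 1.89 | 0.09–0.10 (0.095) |
| 10% | all | 1.80 | 2.00 | 0.20 |
| 20% | half | 1.60 | 1.78 | 0.18 |
| 20% | all | 1.60 | 2.00 | 0.40 |

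Against the SE of 0.666, 0.095 is about 0.14 SE, 0.20 about 0.30 SE and 0.40 about 0.60 SE.

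**5. What changes these figures.**

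- *Partial benefit.* If affected children gain e rather than zero, each excess is multiplied by (D − e)/D. With e = 1 it halves.
- *Worse prognosis.* Suppose affected children would score 2 points below the arm's untreated average, and all stop. The remaining children then average 2q/(1 − q) above it. For q = 10% the available-data value is 2 + 0.2/0.9 = 2.22, an excess of 0.42. For q = 5% and 20% the excess is 0.21 and 0.90.

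**6. CACE analyses.** With equal prognosis and no effect without delivery, the effect and the compliance share are inflated by the same factor 1/(1 − qw), which cancels in the ratio. These analyses are therefore disturbed only if those who stop differ in prognosis.

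**The case against.** The strongest reply is that the rule removes nobody. It is a fallback after replacement has been sought, and it leaves the choice with the participant. It can even be read as protecting data, since it does not treat loss of delivery as withdrawal. Parents in either arm may leave follow-up at any time. The default of seeking outcomes for all Focal children is already stated, and the wording does not say that the child's TPS, rather than the parent questionnaires, would stop. Sensitivity analyses under different missing-data assumptions are planned. A child lost only at 35–40 weeks still contributes a 15–20-week score.

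The event may also be rare. The protocol expects roughly one assistant per participating child, so one departure would affect about one child. With 44 × 4.55 ≈ 200 intervention children, 10% means about 20 of them. The feasibility study is described as having good completion.

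Much of this stands. A reader might infer that the rule excludes undelivered children, or that it defeats the intention-to-treat analysis. The text supports neither reading: it asks a question, the analysis principle is stated, and nothing shows how often the question would be put or how families would answer.

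What remains is that a prompt to reconsider data collection is not the same as a standing right to withdraw, and it comes in one arm, after non-delivery. The planned sensitivity analyses can explore the consequences but cannot recover outcomes that were never collected.

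**Conclusion.** The point holds as a risk of bias, not as a demonstrated one. The protocol opens a route to missing outcomes that in practice exists only in the intervention arm and depends on non-delivery. This sits badly with its own follow-up and analysis principles, and the primary model would not correct for it. If affected children gain less than the others, the direction favours E-PLAYS.

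The size cannot be determined from the document. The range of 0.05–0.20 points (5–10% affected, half to all stopping) and of 0.18–0.40 points (20% affected) rests on assumed rates, no effect without delivery and equal prognosis. Partial benefit would shrink it and worse prognosis would enlarge it. Unless non-delivery is common the bias is modest beside the standard error. The change is worth making because it is cheap and removes an avoidable difference between the arms.

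**What to change.** Replace the second sentence of Teaching assistant retention and withdrawal with: *Where a teaching assistant cannot be replaced, all outcome assessments continue as scheduled unless the parent or carer asks to stop them.* This carries over the separation already made for parent and carer withdrawal.

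Report missing TPS data by arm and, within the intervention arm, by number of sessions received. No new recording is needed, because the E-PLAYS software already logs sessions for each child.

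The cost is one sentence in the protocol and in staff instructions. The assessments are already scheduled, and families keep the right to withdraw at any time.

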### Randomisation

The trial will be cluster-randomised to prevent within-school contamination. Schools will be allocated to intervention or control group using minimisation based on geographical location and proportion of children with free school meals (a proxy for deprivation) by a trial statistician at York Trials Unit using dedicated software (MinimPY [25]). Randomisation will occur following baseline data collection. Schools will be informed of their allocation via email. Schools will be advised to tell the parents/carers of participating children the schools random allocation.

Children in schools allocated to the intervention group will receive E-PLAYS plus whatever constitutes care as usual in their school. Participating children in schools allocated to the control group will receive whatever constitutes care as usual in their school. ‘Care as usual’ is defined as the existing support routinely provided for a child with social communication difficulties from educational and health services.

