### Setting

The trial will take place in state-funded mainstream primary schools and state-funded special primary schools in Bedfordshire, Hertfordshire and North London. Following slightly lower than anticipated recruitment during the internal pilot phase, primary schools in Buckinghamshire will also be recruited for the main trial.

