### School eligibility

#### Inclusion criteria:

A state-funded infant or primary school or special needs school based in the target recruitment areas;

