### Child eligibility (Partner children)

Partner child eligibility criteria are as follows:Children aged 5–7 years old;Children who do *not* meet the criteria for social communication difficulties as determined by the Social Communication Behaviour Checklist [24];Children whose parent/carers give consent for them to take part in the E-PLAYS-2 trial.

Not all Partner children will complete assessments. We will randomly select one Partner child from each school to complete the Test of Pragmatic Skills (TPS) at baseline and follow-up assessments (see details of the TPS below). This will allow for a comparison of the outcomes in this subsample of typically-developing children between intervention (where the child will partner a participating child in E-PLAYS-2) and control schools (care as usual). Parents/carers of the Partner children will be asked to consent to the Partner child completing the TPS (although only one randomly selected participant in each school will complete these assessments as stated above).

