### Primary outcome analysis (focal children)

The planned primary analysis model will include all available post-randomisation TPS [26] scores as outcomes, modelling these measurements using a linear mixed effect model. This model will include fixed effects for treatment group, time point, and their interaction, and will also condition on fixed effects for baseline TPS mean composite score, year group, child FSM status, geographical location of school, and school level random intercepts. Correlation between repeated measurements within participants will be modelled using an unstructured covariance matrix for the model residuals. Precise details of the terms included in the model will be provided in the SAP (including plans for dealing with any incomplete baseline covariate data). If the fit of the planned primary analysis model is reasonable (see below), then the fitted model will be used to estimate differences (Intervention – Control) in expected TPS scores at both post-randomisation time points, together with 95% confidence intervals and p-values for tests of H_0_: $$\delta$$ = 0 (where $$\delta$$ is the difference in expected score at the relevant time point).

The appropriateness of key model assumptions will be checked using diagnostic plots based on the standardised residuals from the fitted model. If these plots (or indeed other extra-data considerations) suggest the observed data show important departures from the assumptions of the planned analysis, then we will undertake semi-parametric analyses of the scores at each post-randomisation time point in isolation. This will be accomplished using cumulative probability models based on ordinal regression [36]. The ordinal regression models will include fixed effects for treatment group, baseline TPS [26] mean composite score, year group and child FSM status, and a random intercept for school.

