### Case study schools

Eight intervention schools (four from the internal trial and a further four from the main trial) will be purposively sampled to act as case studies [38]. Schools will be profiled to include at least the following: one special needs and one mainstream school plus one school with high levels of deprivation and another with a high proportion of children with English as an additional language. These schools will be approached to be case studies before the E-PLAYS intervention is given to them and will continue to be observed throughout intervention delivery. The following assessments will take place with a subgroup of case study participants:Structured observations of the children (Focal and Partner) and teaching assistants as they use E-PLAYS, based on an observation schedule developed for the E-PLAYS feasibility study ([17] mid-intervention);Focus groups conducted with teaching assistants exploring their experiences of delivering E-PLAYS (end intervention);Interviews with the children (Focal and Partner) with a card sorting task and visual analogue scale to give an indication of their liking of E-PLAYS (mid-intervention);Structured interviews with parents exploring the extent to which children play computer games at home before and after the intervention and any changes to game-playing (baseline and 40-week follow-up);

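### Mainstream and special schools are pooled, but school type is neither a minimisation factor nor in the stated primary covariate set: a modest, avoidable loss of precision

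*Protocol article*

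**What the plan says.** The Setting section places the trial in "state-funded mainstream primary schools and state-funded special primary schools in Bedfordshire, Hertfordshire and North London", with Buckinghamshire added for the main trial. The school inclusion criterion agrees: "A state-funded infant or primary school or special needs school based in the target recruitment areas". Neither gives an expected number, quota or cap for special schools.

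The Randomisation section allocates schools "using minimisation based on geographical location and proportion of children with free school meals (a proxy for deprivation". It also defines care as usual as the support a child routinely receives from educational and health services, so its content may vary by school.

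Under Primary outcome analysis (focal children), the model has treatment group, time point and their interaction, and will "condition on fixed effects for baseline TPS mean composite score, year group, child FSM status, geographical location of school, and school level random intercepts". The ordinal fallback model in the same section has treatment, baseline TPS, year group, child free-school-meal status and a school random intercept. The CACE models reuse the primary covariates, and the secondary-outcome models are described as similar. None of them names school type.

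Exact model terms are left to the SAP. The Sensitivity analyses section promises alternative adjustment sets without naming them.

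**The concern.** School type is a fixed property of the randomised unit, known before allocation. It could plausibly relate to how far a child's TPS score moves over 35–40 weeks, through the pupils enrolled, the staffing and the usual provision. The plan itself treats it as a context worth representing when case-study schools are chosen: "one special needs and one mainstream school plus one school with high levels of deprivation". That is only supporting evidence, because it concerns purposive sampling for the process evaluation and names other school characteristics too.

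If special schools are a small minority, an uneven split between arms is quite likely. Any difference in progress between school types, given baseline, then either moves the estimate in the trial as realised or adds to the between-school variation behind the standard error. These are two views of one cost. Planned power has already come down from 90% to about 85.2%, so a recorded prognostic factor that costs almost nothing to include is worth using.

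**Working it through.** **Inputs from the protocol article (Sample size calculations).** 44 schools per arm; 4.55 Focal children per school at randomisation; 20% attrition; SD 7; pre-post correlation 0.6; school-level ICC 0.05; target difference 2 points; two-sided 5%; stated power 85.2%.

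**Step 1: reproduce the stated power.**
- Residual variance = 49 × (1 − 0.6²) = 31.36 (SD 5.6).
- Analysed children per school = 4.55 × 0.8 = 3.64; per arm = 44 × 3.64 = 160.16.
- Design effect = 1 + (3.64 − 1) × 0.05 = 1.132.
- Variance of the effect = 2 × 31.36 × 1.132 / 160.16 = 0.4433; SE = 0.666.
- Power = Φ(2/0.666 − 1.96) = 85.2%. This agrees with the protocol.

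**Step 2: assumptions the protocol does not supply.** Let k be the number of special schools among 88 and d the special-versus-mainstream gap in TPS at 35–40 weeks that remains after baseline adjustment. I take k = 2, 4, 8 and d = 2, 3, with equal cluster sizes. For scale, the protocol equates 2 points with a third of a year, or 6 points a year, so expected progress over 35–40 weeks is 6 × 35/52 = 4.0 to 6 × 40/52 = 4.6 points.

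**Step 3: effect on power.** With p = k/88, school type contributes p(1 − p)d² to the between-school variance and 4/88 of that to the variance of the effect. The planned between-school variance is 0.05 × 31.36 = 1.57. Two cases bracket the result: the contribution comes on top of the planned ICC and is not adjusted for, or it lies within the planned ICC and is removed by adjustment.

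| k | d | Between-school variance | Added to 0.4433 | Power if on top | Power if within and adjusted |
|---|---|---|---|---|---|
| 2 | 2 | 0.089 | 0.0040 | 84.9% | 85.5% |
| 2 | 3 | 0.200 | 0.0091 | 84.5% | 85.9% |
| 4 | 2 | 0.174 | 0.0079 | 84.6% | 85.8% |
| 4 | 3 | 0.390 | 0.0178 | 83.8% | 86.6% |
| 8 | 2 | 0.331 | 0.0150 | 84.0% | 86.3% |
| 8 | 3 | 0.744 | 0.0338 | 82.5% | 87.8% |

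The change from 85.2% is therefore about 0.3 to 2.7 percentage points in either direction.

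**Step 4: how likely and how large an imbalance is.** Treating the split of k schools over 44 and 44 as hypergeometric (minimisation on location and free-school-meal proportion is assumed not to balance school type indirectly):
- Net difference of 2 or more schools: 49% for k = 2, 62% for k = 4, 71% for k = 8.
- Net difference of 4 or more: impossible for k = 2, 12% for k = 4, 27% for k = 8.

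A net difference of 4 shifts the estimate by (4/44) × d, which is 0.18 points for d = 2 and 0.27 for d = 3. That is 9% to 14% of the 2-point target, or 0.27 to 0.41 of the SE.

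**The case against.** The strongest reply is that the model already does most of the work. Baseline TPS is a covariate, with correlation assumed to be 0.6 and observed at 0.79 for 35–40 weeks in the feasibility trial, so only a difference in progress given baseline is left. Every Focal child, in either school type, passes the same checklist, which narrows the contrast. The ICC of 0.05 was set to cover all levels of clustering, against a feasibility value below 0.01, so the on-top column is the pessimistic one. Both k and d are assumed, and d = 3 is about two thirds of expected progress over the follow-up. All of this stands, and it is why the effect is modest.

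A second reply is that the SAP, not shown, may add school type. That is possible, but the article names a covariate set for the primary model, and unnamed sensitivity sets would leave the primary estimate unchanged. Choosing two minimisation factors is a normal design judgement.

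A reader might also infer that the Partner analysis is compromised, because it is a "comparison of the outcomes in this subsample of typically-developing children between intervention" and control schools yet draws one Partner from every school, special schools included. The document does not support this. Every Partner, in any school, must not meet the checklist criteria for social communication difficulties, and the analysis is declared exploratory. No change to it is needed on this account.

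**Conclusion.** The omission is real: two school types are eligible, and neither the minimisation nor the stated primary covariate set includes school type. The consequence is some loss of precision and of accuracy conditional on the realised split.

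A reader might go further and infer that the effect estimate will be biased, that type I error is inflated, or that the stated power is wrong. The document supports none of these. Chance imbalance under randomisation does not bias the estimator over repeated allocations, the random intercept passes residual school variation into the standard error, and the 85.2% reproduces from its stated inputs. Nor does the article show that special schools will be few or their pupils very different on the TPS; those are assumptions here.

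On those assumptions (2 to 8 special schools, residual gap 2 to 3 points), the stake is the modest range of power and shift shown in the working. It is smaller if only one or two special schools enrol. The point is an inexpensive improvement, not a flaw that threatens the trial's conclusion.

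**What to change.** Pre-specify school type (mainstream or special) as a fixed effect in the primary Focal-child model. Name it explicitly in the CACE, secondary-outcome and fallback ordinal models as well; the fallback needs its own statement because its listed covariates already differ from the primary set (it omits location). Report the number of special schools per arm.

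If too few special schools enrol for the term to be estimable, name school type as one of the alternative adjustment sets under Sensitivity analyses, and fix that rule before outcome data are seen by arm.

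Adding school type to the minimisation for schools still to be randomised is optional. The 20 internal-pilot schools have already been randomised, so this would be a mid-trial change to allocation that requires those schools to be coded retrospectively.

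The cost is a line in the protocol and SAP and about one degree of freedom at school level (with 88 schools in two arms, 86 before covariates). School type is known at recruitment, so no new data are needed. The downside is little gain if very few special schools take part.
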